§Patients randomised to group B will receive specific advice on the amount of fluid required per day to reduce the urine osmolality to ≤270 mOsmol/kg. Patients in group B will be asked to self-monitor their USG regularly at home using urine dipstick (provided to the patients), and adherence to the intervention will be quantified by patient responses to SMS text, sent twice weekly during months 0–6 and then monthly for the duration of the study, asking for the results of that day’s USG.

¶All patients will conduct two 24 hours urine collections and record their fluid intake for those 2 days prior to baseline visit. The study dietitian will provide group B patients with diet and fluid assessments and review during all study visits to ensure prescribed fluid intake is achieved and to validate a fluid intake tool.

**To be collected following the screening visit and prior to the final visit (two collections each).

††To be collected between study visits (one collection only).

‡‡To be collected prior to the study visit (one collection only).

§§To be collected at screening for *PKD* gene analysis.

¶¶To be collected at all study visits for exploratory renal biomarkers (stored at −80°C).

ADPKD, autosomal dominant polycystic kidney disease; AE, adverse event; BP, blood pressure; PKD, polycystic kidney disease; SMS, short message service; USG, urine-specific gravity.

### Measures to reduce bias

The trial intervention is an unblinded behavioural modification. Bias and contamination could be introduced by a participant’s expectations and prior knowledge of the hypothesised role of fluid intake in ADPKD. To minimise the effect of this problem:Both groups will be educated about the fact that fluid requirement in ADPKD is not known and that the intervention may be equally beneficial. The patient information consent form has been written in an objective, neutral manner to accurately reflect current evidence, and does not discuss the hypothesised benefits of fluid intake in ADPKD.Appointments will be scheduled for the two study groups at different times of the day to minimise the chance of control group participants meeting the intervention group in the waiting room.Outcome assessors will be blinded to participants’ treatment allocations.

### Sample size calculation

In longitudinal data from the CRISP-II cohort, the average rate of increase in ht-TKV was 5.5% per year (SD, 3.8% per year; n=201; 8-year follow-up). Preclinical and clinical studies using pharmacological inhibition or adequate hydration to inhibit ADH-mediated cyst growth resulted in similar treatment efficacy of ~50% lesser increase in kidney volume.^10^ In this trial, a more modest (but still clinically important) treatment effect of 35% is nominated. Using these assumptions, a total sample size of 150 will have 87% power to detect a difference in ht-TKV of 1.9% per year, using a two-sided test and a 0.05 level of significance. Taking into account the possibility of 15% dropouts, our aim is to include 180 participants (n=90 per arm).

The estimation of dropouts was based on experience from previous clinical trials in ADPKD. Furthermore, it was suspected that there would be significant interest for participants to remain in this study due to the low risk of AEs with the intervention; as well as the strong interest and motivation expressed by patients with PKD at the study centres, in part due to genetic nature of the disease and the paucity of opportunities for clinical research in PKD in the past. In reality, however, the exact proportion of subjects that dropout and/or withdraw from the intervention (protocol deviation) will not be known until the trial has concluded, and is a secondary outcome measure to assess the efficacy of the intervention.

### Statistical methods and data management

Intention-to-treat principles will be followed. Patient characteristics (age, sex, ht-TKV, eGFR) will be compared at baseline, and analysis of covariance will be used to analyse log_10_ ht-TKV at months 18 and 36, with baseline log_10_ ht-TKV as the covariate. Assumptions of the analysis of covariance of normally distributed residuals and constant variance will be assessed with normal probability plots and residual versus fitted plots. Linear mixed-effects models will be used to test the interaction between treatment groups and time, if assumptions of equal covariance between times cannot be guaranteed. The adherence distribution will be constructed in the intervention arm by using the proportion of times a subject responds to the SMS. Outcome measure will be transformed to appropriate normality if required, and the Χ^2^ test or Fisher’s exact test will be used to test the association between categorical variables. The data management plan and the electronic case report forms have been developed in the OpenClinica platform, harmonised using National Institutes of Health-Clinical Data Interchange Standards Consortium (NIH-CDISC) terminology for ADPKD to enable future data sharing.^44^ The Research Data Storage Plan has been approved by University of Sydney.

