## Methods and analysis

### Participants, design and registration

This is a prospective, parallel-group, open-label, multicentre randomised controlled trial, which will enrol 180 participants that meet the inclusion criteria (table 1). The planned recruitment period is up to 1.8 years, and began at Westmead Hospital in December 2015. For participants, the duration of the trial is 3.2 years, including the screening visit and the run-in, treatment and post-treatment periods (figure 1). The trial is registered (Australian New Zealand Clinical Trials Registry number 1261-4001-216-606) and will be conducted according to Good Clinical Practice and reported using Consolidated Standards of Reporting Trials guidelines.^25^

**Table 1 T1:** Inclusion and exclusion criteria

Inclusion criteria	
1.	Adult patients providing informed consent, aged 18–65 years of age
2.	Diagnosis of ADPKD, such as meeting the Pei-Ravine criteria^52^
3.	eGFR (CKD-EPI) ≥30 mL/min/1.73 m^2^ within 6 weeks of randomisation
Exclusion criteria	
1.	Safety risk, eg, serum Na^+^ <135 mmol/L; requirement for medications with high risk of precipitating hyponatraemia, such as chronic use of diuretics; medical conditions that require fluid restriction, such as heart failure, chronic liver disease, nephrotic syndrome or generalised oedema; abnormalities in the voiding mechanism; pregnant or breastfeeding women
2.	Contraindication to or interference with MRI assessments (eg, ferromagnetic prostheses, aneurysm clips, severe claustrophobia or other contraindications)
3.	Risk of non-compliance with trial procedures (eg, history of non-compliance with medical therapy; history of substance abuse within the previous 2 years and/or participants who do not complete the required screening tests (24 hours urine, blood tests and baseline MRI) within 12 weeks of the screening visit)
4.	Concomitant conditions or treatments likely to confound end point assessments (eg, poorly controlled diabetes, other known causes of CKD, renal cancer, single kidney or severe comorbid illnesses)
5.	Participation in other clinical trials to slow ADPKD or CKD
6.	TKV Mayo Clinic subclass 1A on screening (low risk of progression)^53^

ADPKD, autosomal dominant polycystic kidney disease; CKD, chronic kidney disease; CKD-EPI, Chronic Kidney Disease Epidemiology Collaboration equation; eGFR, estimated glomerular filtration rate; TKV, total kidney volume.

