
### Randomisation procedure

Participants will be randomly allocated in a 1:1 ratio (in permutated blocks of 4) to the control group or the intervention group, stratified by baseline eGFR (<60 or ≥60 mL/min/1.73 m^2^). Randomisation and concealed allocation will be performed with a secure, web-based randomisation service (Randomize.net). The trial statisticians have generated a validated randomisation list.

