### Primary end point

The primary end point is the percentage annual change in height-adjusted total kidney volume (ht-TKV) from baseline to 36 months as determined by serial MRI. Dialysis-dependent kidney failure takes decades to develop in ADPKD, making it impractical to use serial changes in serum creatinine and eGFR for assessing treatment efficacy. Ht-TKV is a highly sensitive surrogate marker that measures exponential cyst growth, the key parameter of ADPKD progression and has been used as a primary end point in many pivotal clinical trials. The longitudinal Consortium for Radiologic Imaging Studies of PKD (CRISP-I) study established that the rate of increase in TKV is relatively constant (~5.6 %/year) and can be quantified with high precision by MRI (reliability coefficient, 0.998; mean coefficient of variation, 0.01%).^2^ In CRISP-II, adjusting for height reduced variability in TKV, a baseline ht-TKV value of >600 mL/m predicted development of CKD stage 3 over an 8-year period (area under the curve=0.84; sensitivity, 74%; specificity, 75%).^38^ The magnitude of the rate of increase in ht-TKV predicted the risk of ESKD.

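### Randomisation is stratified by baseline eGFR, but neither the primary ANCOVA nor the fallback mixed model is described as including that stratum

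*Protocol article*

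**What the plan says.** Under Randomisation procedure, participants are "randomly allocated in a 1:1 ratio (in permutated blocks of 4") and allocation is "stratified by baseline eGFR (<60 or ≥60 mL/min/1.73 m^2"). This is the only stratification factor named.

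Under Primary end point, the outcome is the "percentage annual change in height-adjusted total kidney volume (ht-TKV) from baseline to 36 months".

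Under Statistical methods and data management, "analysis of covariance will be used to analyse log_10_ ht-TKV at months 18 and 36", "with baseline log_10_ ht-TKV as the covariate". One covariate is named, in the singular. eGFR appears in that section only among the characteristics to be compared at baseline. The alternative model is described as follows: "Linear mixed-effects models will be used to test the interaction between treatment groups and time", to be used if equal covariance between times cannot be assumed. No stratum term is given for it either.

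**The concern.** Stratified blocks force the arms to be nearly balanced on the eGFR stratum. If the stratum is prognostic, this balance makes the treatment difference less variable from trial to trial than under simple randomisation. A model that leaves the stratum out does not recognise this. It keeps the between-stratum variance in the residual, so the reported standard error exceeds the true sampling variability.

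The result is an interval that is too wide and a test that rejects less often than 5% under the null. The point estimate is unaffected on average. What is at stake is calibration and a little precision in a trial planned on 150 evaluable participants. There is also a plain design principle: the analysis should reflect the restriction placed on the randomisation.

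**Working it through.** **Inputs from the Protocol article (Sample size calculation).** Growth 5.5% per year with SD 3.8% per year; relative effect 35%; 150 evaluable participants (75 per arm); difference 1.9% per year; two-sided 0.05; stated power 87%.

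**Inputs assumed.** The share R² of growth variance that the eGFR stratum explains beyond baseline ht-TKV is not given, so 0, 5% and 10% are shown. The smaller stratum is assumed to hold 30% of participants.

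**Step 1: reproduce the stated power.**
- SE = 3.8 × √(2/75) = 0.621.
- Normal approximation: 1.9/0.621 = 3.06, and Φ(3.06 − 1.96) = 86.5%.
- With the unrounded difference, 0.35 × 5.5 = 1.925, power is 87.3%.
- With the noncentral t distribution the two values are 86.0% and 86.9%.

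The 87% reproduces. It uses an SD that takes no credit for any covariate.

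**Step 2: what omission does, by formula.** With the stratum balanced by design, the true sampling SD of the difference is about 3.8 × √(1 − R²) × √(2/75), while the model without the stratum still reports about 0.62.
- R² = 5%: true SD 0.605. Type I error ≈ 2 × [1 − Φ(1.96/√0.95)] = 2 × [1 − Φ(2.011)] = 4.4%.
- R² = 10%: true SD 0.589. Type I error ≈ 2 × [1 − Φ(1.96/√0.90)] = 2 × [1 − Φ(2.066)] = 3.9%.

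**Step 3: simulation.** 6,000 trials of 150 participants, blocks of 4 within a binary stratum, outcome on the growth-rate scale with total SD 3.8, true difference 1.9.

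| R² of stratum | Model | True sampling SD | Mean model SE | Type I error | Power |
|---|---|---|---|---|---|
| 0 | without stratum | 0.617 | 0.619 | 4.9% | 86.2% |
| 0 | with stratum | 0.617 | 0.619 | 4.9% | 86.2% |
| 5% | without stratum | 0.609 | 0.620 | 4.7% | 86.4% |
| 5% | with stratum | 0.609 | 0.605 | 5.2% | 87.7% |
| 10% | without stratum | 0.590 | 0.620 | 4.0% | 87.3% |
| 10% | with stratum | 0.590 | 0.588 | 5.2% | 89.5% |

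The simulation error on a 5% rate is √(0.05 × 0.95/6000) = 0.28 points. The simulated 4.7% and 4.0% therefore agree with the formula values of 4.4% and 3.9%, and the 5.2% values are compatible with 5%.

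**Reading.** Without the stratum the model SE stays near 0.62 whatever the truth is. With the stratum it tracks the true variability. The power gain is 1.3 points at 5% (87.7 − 86.4) and 2.2 points at 10% (89.5 − 87.3).

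**Limit of the calculation.** R² is meant as a share of what remains after baseline ht-TKV, but it is applied to 3.8, which the article reports as a cohort SD with no mention of such adjustment. The figures show the order of magnitude and do not forecast this trial.

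**The case against.** **The effect is conditional.** Nothing in the article shows that eGFR, cut at 60, predicts ht-TKV growth once baseline ht-TKV is in the model. eGFR probably overlaps with kidney volume, and the Primary end point section describes growth as fairly steady. This stands. A reader might infer that the standard error is definitely too large; the documents support only that it would be if the stratum is prognostic.

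**No planned power is lost.** This also stands. The 87% rests on an SD without covariate adjustment, so any gain from the stratum comes on top. A reader might infer that the sample size is wrong or that type I error is inflated. Neither follows; the departure is in the conservative direction.

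**The article is a summary.** Its timeline table records that a biostatistical management plan was developed, and that plan may add the stratum. This weakens the point but does not remove it, because the article is not silent on covariates: it names one, in the singular. If a fuller plan includes the stratum, the published text needs to be aligned with it.

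**Mayo class.** The eligibility table excludes "TKV Mayo Clinic subclass 1A on screening (low risk of progression"), so a reader might infer that leaving Mayo class out of the model is a second error of the same kind. It is not. Mayo class is not a stratification factor, so the standard error without it is valid and only possible precision is forgone. Nor does the article say that a full subclass is recorded for each participant, and the class overlaps with kidney volume already in the model. Larger gains obtained by pooling Mayo class or age with the stratum need an assumed R² that the documents do not give, and they do not measure the omission of the stratum.

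**Conclusion.** The point holds in a limited form. The stated primary model and its fallback do not include the one factor used to stratify the randomisation. If that factor is prognostic beyond baseline ht-TKV, the analysis is slightly conservative: at an assumed 5% to 10% of variance, type I error is about 4.7% to 4.0% and about 1 to 2 points of available power go unused. If it is not prognostic, omission costs nothing and inclusion costs a negligible amount. The estimate is not biased and the sample size stands. The direction follows from the design; the size rests entirely on the assumed R², the assumed 30% in the smaller stratum, and the use of 3.8 as the SD. This is an inexpensive improvement and does not threaten the trial's validity.

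**What to change.** State in the analysis plan that the primary ANCOVA of log10 ht-TKV includes the randomisation stratum (eGFR below 60, or 60 and above) together with baseline log10 ht-TKV. In the mixed model, include the stratum and its interaction with time: a main effect alone shifts only the level of kidney volume, whereas the end point is its growth. Keep the model without the stratum as a sensitivity analysis.

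The cost is one sentence, one degree of freedom in the ANCOVA and two fixed-effect terms in the mixed model. The stratum is known for everyone at randomisation, so no new data are needed. The choice should be fixed before outcome data are compared by arm.

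Optionally, if the full Mayo subclass is recorded at screening, it may be prespecified as a further covariate for precision. That is a separate choice and is not needed to correct this point.

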Total solutes (urine osmolality×urine vol (mL)) is the mean derived from two 24 hours urine samples collected between the screening visit and the randomisation/baseline visit.*Dietary counselling*. A high dietary solute load (due to high salt and protein intakes) requires a higher fluid intake to maintain urine dilution.^11^ Participants will be educated about the importance of dietary solute intake in determining obligatory urine volume (ie, the minimum urine volume required to excrete the daily solute load).^32^ The study dietitian will take a detailed diet history and provide tailored dietary advice to enable participants to achieve and maintain a moderate protein intake (0.75–1.0 g/kg/day) and limit sodium intake to 80–100 mmol/day.^19^ If the calculated prescription is >3 L/day, the participant will be advised to gradually increase fluid intake until target urine osmolality is reached and focus on reducing dietary solutes to reduce the risk of hyponatraemia.*Review of lifestyle and environmental factors*. The participant’s lifestyle, personal preferences and occupation will be recorded and reviewed when providing individualised techniques for promoting adherence to fluid intake. Participants will be provided with 3×1 L reusable water bottles to help keep track of their fluid intake, and will be encouraged to drink evenly throughout the day and replenish with each episode of nocturia.*Self-monitoring of fluid intake and treatment efficacy*. Aids have been developed to assist participants with self-monitoring, including a paper-based diary or web-based/smartphone compatible tool to self-monitor fluid intake, and urine dipsticks will be provided to record urine-specific gravity (USG). Participants will be shown how to read their USG and will be asked to test it during the late afternoon (16:00–20:00 hours) at least once daily in the first 2 weeks of the study, at least twice weekly for the first 6 months and then at least monthly for the duration of the study. An USG of ≤1.010 indicates a spot urine osmolality of ≤270 mmol/L, meaning that fluid intake in the past few hours has been adequate. Participants will also be briefed on receiving and responding to short message service (SMS) text messages (or emails if they do not own a mobile phone) requesting the results of a late afternoon USG measurement (see below), as well as on the schedule of telephone calls (see below).*Scheduled telephone calls and follow-up study visits*. Participants in the intervention group will be contacted by telephone (at weeks 1, 3 and 6, then monthly in year 1, and 3-monthly for years 2–3) and reviewed face-to-face at all study visits by the Study Dietitian to assess compliance with fluid intake, discuss USG results, ensure that blood and urine samples are collected and to record any AEs and new medications commenced. If necessary, the fluid prescription will be adjusted depending on the results of progress 24 hours urine osmolality and USG. The study dietitian will monitor compliance with protein and sodium recommendations using 24 hours recalls at all study visits.*Response to SMS text messages*. To provide a quantitative measure of adherence, participants in the intervention group will be required to reply (within 12 hours) to an SMS message requesting the results of a late afternoon USG. The SMS message will be delivered randomly twice a week in months 0–6, then monthly for the duration of the study.*Rationale for the intervention*. Previous trials in patients with recurrent nephrolithiasis in Italy and Israel have shown that a long-term increase in fluid intake can be achieved with targeted education provided at clinic visits alone^33 34^ but, for the current study in Australia, telephone coaching by a dietitian and the above tools are included to boost compliance and continued participation.^35^ A systematic review revealed that self-monitoring of USG is a critical tool to enhance the implementation of increased fluid intake in clinical trials.^36^ SMS texting is a method preferred by consumers in health interventions.^37^

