### Secondary end points

*Systemic AVP activity*. Markers will be serum copeptin,^5 24^ 24 hours urine osmolality and volume.*Kidney disease progression*. Markers will be rate of eGFR decline (0 and 3 to 36+ months); resting mean arterial pressure; urine albumin-to-creatinine ratio and kidney pain as assessed by the HALT-PKD questionnaire.*Treatment adherence*. Measured by proportion of the intervention group responding within 12 hours to SMS texts requesting results of the late afternoon USG; proportion of the intervention group with 24 hours urine osmolality ≤270 mOsmol/L.*Safety end points*. Measured by proportion of participants with serum Na^+^ <130 mmol/L; episodes of serious AEs (SAEs).*Patient acceptability*. Measured by a Treatment Acceptability questionnaire^39^ and the proportion of participants withdrawing from the study.*Quality of life*. Measured by the Kidney Disease Quality of Life short form (KDQOL-SF) 1.3 tool.*Healthcare utilisation*. At each study visit, participants are asked if have had any new diagnosis, hospital visits, seen a general practitioner or changed medication since the previous visit.

Study end points were developed to ensure that appropriate health economic analyses can be undertaken at the conclusion of the trial. Future linkage with the Australian and New Zealand Dialysis and Transplant Registry will enable long-term outcomes (eg, time to reach ESKD) to be determined with minimal cost.

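### The SMS adherence measure counts a reply whatever urine-specific gravity it reports and, if messages are pooled, draws about 63% of its weight from months 0–6

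*Protocol article*

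**What the plan says.** The article sets up the SMS measure under Study intervention (group B): "To provide a quantitative measure of adherence, participants in the intervention group will be required to reply (within 12 hours) to an SMS message" that asks for a late-afternoon USG result. The schedule is given there too: "The SMS message will be delivered randomly twice a week in months 0–6, then monthly for the duration of the study". The randomisation footnote to the schedule of assessments (Table 2) also has adherence quantified by the responses to these texts.

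Under Secondary end points, treatment adherence has two components. One is the "proportion of the intervention group responding within 12 hours to SMS texts requesting results of the late afternoon USG". The other is the "proportion of the intervention group with 24 hours urine osmolality ≤270 mOsmol/L".

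Statistical methods and data management carries only the first component forward: "The adherence distribution will be constructed in the intervention arm by using the proportion of times a subject responds to the SMS". That sentence mentions neither the 12-hour limit nor the value reported.

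The self-monitoring text under Study intervention (group B) does give a criterion for the value: "An USG of ≤1.010 indicates a spot urine osmolality of ≤270 mmol/L, meaning that fluid intake in the past few hours has been adequate". No description of the SMS measure uses it.

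**The concern.** The intervention is drinking enough to dilute the urine to a set target. A measure that scores only whether a text was answered can move independently of that. A participant who always answers promptly with an off-target value gets full marks, while one who drinks as prescribed but ignores half the texts gets half marks. The message asks for the value, and the rule then ignores it.

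The second problem is weight. The message rate drops sharply after month 6, so a simple proportion of messages answered mostly describes the first half-year of a three-year intervention. Contact is also most intense then: telephone calls thin out from monthly in year 1 to 3-monthly in years 2–3, and the minimum USG self-testing falls to monthly after month 6. A later fall in replies is therefore plausible, and a pooled figure would partly hide it.

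At stake is a named secondary end point and how it is read beside the primary result. Under Outcomes and significance, the article expects a negative result from a properly performed study to settle the question. That argument needs evidence that the intervention group stayed near target for three years.

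**Working it through.** The article states no figure for the weighting of messages, so there is none to reproduce first.

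**Reply against value.** Inputs: the reply rule (Secondary end points; Statistical methods and data management) and USG ≤1.010 (Study intervention, group B). Take 82 messages per participant, as derived below.

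- Participant A answers every message within 12 hours and always reports 1.025. Stated rule: 82/82 = 100%. Replies at target: 0/82 = 0%.
- Participant B is always at or below 1.010 but answers half the messages. Stated rule: 41/82 = 50%.

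The rule ranks A above B, although only B reaches the target. This holds however the messages are weighted.

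**Weight of the first six months.** Inputs: two messages a week in months 0–6, then one a month (Study intervention, group B), with 36 months of treatment (Study visits).

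- Months 0–6: 26 weeks × 2 = 52 messages.
- Months 7–36: 30 × 1 = 30 messages.
- Share of messages from months 0–6: 52/(52 + 30) = 63.4%. Taking 24 to 26 weeks and 29 to 31 monthly messages gives 61% to 64%.
- Share of treatment time: 6/36 = 16.7%.
- Over-weighting: 63.4/16.7 = 3.8-fold.

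**Effect on the summary.** Let e be the reply rate in months 0–6 and l the rate afterwards.

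- Pooled = (52e + 30l)/82.
- Time-weighted = (6e + 30l)/36.
- Difference = (52/82 − 6/36) × (e − l) = 0.467 × (e − l).

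The article gives no reply rates, so the rates below are assumptions that span the possible directions.

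| e | l | Pooled | Time-weighted | Difference (points) |
|---|---|---|---|---|
| 90% | 90% | 90.0% | 90.0% | 0 |
| 90% | 70% | 82.7% | 73.3% | +9.3 |
| 90% | 50% | 75.4% | 56.7% | +18.7 |
| 90% | 30% | 68.0% | 40.0% | +28.0 |
| 60% | 80% | 67.3% | 76.7% | −9.3 |

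The pooled figure is too high only when replies decline after month 6. It is unaffected when they are stable and too low when they rise.

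**The case against.** The strongest reply is that adherence is not left to text messages. Secondary end points also lists 24-hour urine osmolality at target, which is objective and tied directly to the intervention. Study measurements schedules 24-hour urine at months 3, 6, 9, 12, 18, 24, 30 and 36, so six of the eight on-treatment time points fall after month 6. The section on study limitations says that 24-hour urine results will be used to judge compliance in the intervention group. Copeptin, urine osmolality and urine volume are also secondary end points compared between groups, and they show separation of the arms in a way that one-arm SMS data cannot. All of this stands. A reader might infer that a null primary result could not be interpreted because adherence means only replying. The documents do not support that.

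It can also be said that a reply rate is a legitimate measure of engagement with self-monitoring, that pooling is inferred from one condensed sentence, and that an analysis plan not shown here may split by period. The first is true, but the article labels the measure adherence. The second and third stand as limits on the weighting argument: pooling is the natural reading of a proportion of times, but it is not stated. A reader might also infer that the result is bound to overstate adherence. The sign depends on reply rates that the documents do not give, so only the possibility can be claimed.

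Finally, counting every non-reply as off target would itself partly score texting, and spot USG is self-reported and reflects only the preceding few hours. That is fair, and it shapes the remedy.

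None of this answers the main defect. The reply rule is stated in several places, none of them refers to the value, and it is the only adherence analysis that the statistical section names.

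**Conclusion.** The point holds in limited form. One of the two adherence measures scores replying rather than reaching the plan's own dilution criterion, so it measures engagement. This follows from the stated rule and needs no assumption about rates or weights.

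The weighting part is conditional. If all messages are pooled per subject, months 0–6 carry about 63% of the weight (61% to 64%) for 17% of treatment time. The summary may then overstate long-term adherence, by 0.467 times any fall in the reply rate after month 6. For an assumed fall from 90% to 50% that is about 19 percentage points.

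The consequence is confined to a secondary end point and its interpretation. The primary analysis is untouched, and the 24-hour osmolality measure still allows long-term adherence to be judged. The change is worth making because the messages already ask for the values it needs.

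**What to change.** Under Secondary end points and Statistical methods and data management:

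- Report the proportion of messages answered within 12 hours as engagement, with the same time limit in both sections.
- Define SMS adherence as the proportion of message occasions with a reply within 12 hours and a reported USG ≤1.010.
- Add a sensitivity summary among replies only, because a missing reply does not prove that the participant was not drinking as prescribed.
- Present both measures by period, for example months 0–6, 7–12, 13–24 and 25–36, with an overall figure weighted by time: (6p₁ + 6p₂ + 12p₃ + 12p₄)/36, where p₁ to p₄ are the period proportions.
- Read them beside the proportion with 24-hour urine osmolality ≤270 mOsmol/L, and name that measure as the main evidence of long-term adherence.

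The cost is wording and a little more analysis. No new data are needed, provided the USG values in the replies have been stored. Adherence so defined cannot exceed the 12-hour reply rate and will probably look less favourable. The later periods rest on about 6, 12 and 12 messages per participant, so individual proportions there will be coarse. The measure will still depend on self-reported spot USG.
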